### Objectives {7}

In the current study, we aim to address the following hypotheses:

Primary hypothesis:Delirium incidence is lower in the intervention group than in the control group

Secondary hypotheses:2)Pain intensity is lower in the intervention group than in the control group3)Intraoperative: NOL values are lower in the intervention group than in the control group4)Postoperative: NRS values are lower in the intervention group than in the control.5)Pain medication consumption p.p. is lower in the intervention group than in the control group6)Postoperative nausea and vomiting (PONV) incidence is lower in the intervention group than in the control group

Exploratory analyzation:7)The above-mentioned effects differ depending on whether the subjects hear a speaker’s voice according to their own gender or not

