### Participant timeline {13}

The study duration for all included participants will be defined by the time of surgery until the day of discharge. A follow-up survey of the cognitive function level is planned after 3 months (follow up). The postoperative follow-up point in time was determined by the fact that, at this juncture, patients have customarily concluded their postoperative inpatient rehabilitation and have resided in their domestic environment for a period of several weeks. This period represents the earliest time frame in which daily functioning can be meaningfully assessed, without the confounding influence of ongoing rehabilitation measures or acute postoperative recovery processes. Therefore, it enables a valid evaluation of cognitive performance and its effect on daily living activities under stable conditions. Moreover, the timing of the follow-up assessment is consistent with international recommendations for the evaluation of postoperative POCD and associated outcomes. Evered et al. propose that cognitive testing for POCD should be conducted a minimum of 3 months after surgery, with the aim of avoiding the capture of transient, early postoperative changes [8]. While the MoCA was administered at baseline as an inclusion criterion to confirm adequate cognitive status at 3-month follow-up, no cognitive screening tool was applied. Instead, the assessment focused on functional outcomes using the SF-36 and iADL, as these measures are more directly aligned with capturing everyday functioning. Given the nationwide recruitment, follow-up instruments were selected to allow remote completion and ensure high response rates. Table 1 shows a detailed overview of the course of the study.

**Table 1 Tab1:** Participant timeline

	STUDY PERIOD													
Date	Prior to surgery		Day of surgery						Day 1	Day 2	Day 3	Day 4	Day 5	+3 months
Timepoint	Screening	Baseline	Pre-OP	OP	PostOP recovery room				PostOP ward					Follow-Up
Visit-Code	SCR	V0	V1	V2	V3a	V3b	V3c	V3d	V4	V5	V6	V7	V8	V9
ENROLMENT														
Eligibility criteria	●													
Informed consent	●													
Feedback request	●													
ASSESSMENTS														
MOCA		●												
TMT		●												
Frailty Screening		●												
PONV risk-score		●												
Charlson Comorbidity Index		●												
Permanent medication		●												
QUESTIONNAIRES														
iADL		●												●
SF36		●												●
GDS		●												●
BDI														●
Complications														●

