### Sample size {14}

Based on the primary endpoint analysis, the sample size was calculated as follows:

At the university hospital, LMU Munich, a delirium incidence of approx. 25% can be assumed for electively orthopedic surgery. By means of therapeutic suggestion may be reduced by at least 50%. The calculation in G*Power [24] using the z-test “Difference between two independent proportions” results in a sample size of 110 subjects per group for a design in which the intervention group and control group are of equal size, with a required power of at least 0.8 and a significance level of 5%. This results in a total of 220 subjects.

Based on the results of the study by Nowak et al. 2020 [11], we also calculated the sample size needed to detect effects of the intervention on pain expression, which are of great interest in the secondary endpoint analysis: For effects on opioid use, an effect size of *d* = 0.36 is assumed. For a required power of 0.8 at a level of significance at 5%, a group size of at least 101 subjects is needed. For effects on pain intensity, an effect size of 0.325 can be calculated using G*Power based on the mean values and standard deviations given in the original work. When power is set at 0.8 and significance level at 5%, the resulting sample size amounts to a total of 248 subjects.

In addition to the effect of the intervention on delirium incidence, the effect on pain severity is also of great interest as a (secondary) endpoint. Hence, the larger calculated sample number (*n* = 248) is chosen as a further basis for calculation to be able to achieve sufficiently good power for the secondary endpoints as well.

To ensure that the calculated minimum power will be achieved, there is a need to take possible drop-outs into account. Therefore at least 10% more subjects will be necessary, which results in a total of 273 participants. In consideration of the balanced design, the final target equals in a rounded up total number of 280 patients.

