### Data collection and management

#### Plans for assessment and collection of outcomes {18a}

##### Baseline

Patients will be pseudonymized after inclusion. Required data items encompass Montral Cognitive Assessment (MOCA) [25], Frailty-test [26], PONV risk score [23], and continuous medication including pain medication. Additionally, patients will complete the Quality-of-Life questionnaire (SF-36) [27], Geriatric Depression Scale (GDS) [28], and instrumental Activities of Daily Living (iADL) [29].

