### Statistical methods

#### Statistical methods for primary and secondary outcomes {20a}

To ensure normal distribution, the Kolmogorov–Smirnov test will be conducted prior to further analyses. Statistical significance will be considered at a *p*-value < 0.05. The primary outcome (postoperative delirium incidence) and other binary outcomes (e.g., incidence of postoperative nausea and vomiting, PONV) will first be compared between the intervention and control groups using the chi^2^ test. Continuous non-parametric variables will be analyzed with Mann–Whitney *U* tests, and parametric variables with Student’s *t*-test. To account for potential confounding effects of intraoperative and postoperative medication use, detailed data on the type and dosage of analgesics and sedatives will be collected. These variables will be included as covariates in multivariable logistic regression models for binary outcomes (e.g., delirium, PONV) and multivariable linear regression models for continuous outcomes (e.g., postoperative pain scores, NRS; intraoperative NOL index values). Confounders will be selected a priori based on clinical relevance and evidence from previous literature to avoid data-driven overfitting.

Medication-related parameters (e.g., total opioid dose, intraoperative sedative use) will also be analysed descriptively and compared between groups. Sensitivity analyses will be performed to assess the robustness of the results with and without adjustment for these covariates.

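### Secondary hypothesis 5 (postoperative pain-medication consumption) gets an unadjusted comparison although preoperative pain medication is collected: lost precision, not bias

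*Protocol article*

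**What the plan says.** All references are to the protocol article.

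- **Hypothesis.** Objectives {7} lists as a secondary hypothesis: "Pain medication consumption p.p. is lower in the intervention group than in the control group".
- **Sample size.** Sample size {14} gives this outcome its own calculation: "For effects on opioid use, an effect size of *d* = 0.36 is assumed", and then "For a required power of 0.8 at a level of significance at 5%, a group size of at least 101 subjects is needed". The trial is sized on the larger total of 248 for pain intensity, raised to 280 for dropout.
- **Analysis.** Statistical methods {20a} assigns continuous variables to Student's t-test or the Mann-Whitney U test. On medication as an outcome it adds: "Medication-related parameters (e.g., total opioid dose, intraoperative sedative use) will also be analysed descriptively and compared between groups".
- **Covariates.** The same section plans multivariable models. The covariates it names are analgesic and sedative doses, recorded to deal with drug use during and after surgery. Its examples of continuous outcomes for these models are the NRS and the NOL index. Other confounders are to be fixed beforehand from clinical judgement and published evidence; none is listed.
- **Data available.** The Baseline part of {18a} records "continuous medication including pain medication". Table 1 in Participant timeline {13} also ticks pain-medication consumption at the Pre-OP visit (V1).

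**The concern.** Patients awaiting hip or knee surgery plausibly differ widely in how much analgesic they already take, and some of that difference would carry over into use after surgery. A two-sample test leaves this variation in the error term, so the confidence interval is wider than it need be. Randomisation is stratified by gender only, so a chance excess of preoperative analgesic users in one arm would also stay in the point estimate.

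The adjusted models in {20a} do not fill the gap. For this hypothesis the named covariates are largely the outcome itself, and they arise after randomisation. The one covariate that could sharpen the comparison is already on the case report form but is not named. At stake is the precision of a secondary hypothesis that the plan thought important enough to power separately.

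**Working it through.** **Inputs from the article.** d = 0.36, power 0.8, level 5% and 101 per group for opioid use; effect size 0.325 and a total of 248 (124 per arm) for pain intensity; 1:1 allocation. On the level, {20a} says only "Statistical significance will be considered at a *p*-value < 0.05"; it does not say one-sided or two-sided.

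**Assumed input.** The correlation rho between preoperative use and postoperative consumption. The article gives none, so a range of 0.3 to 0.7 is shown.

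**Step 1: reproduce the plan's figures.** Take the t-test sample size per group and divide by the Mann-Whitney relative efficiency, 3/pi = 0.955.

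- d = 0.36, one-sided 5%: 96.09 / 0.955 = 100.6, so 101 per group. This matches.
- 0.325, one-sided 5%: 117.75 / 0.955 = 123.3, so 124 per group, 248 in total. This matches.
- Variants that do not match: one-sided t-test, 97 and 118 per group; two-sided t-test, 123 and 150; two-sided Mann-Whitney, 128 and 157.

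The planning figures are therefore consistent with one-sided Mann-Whitney tests with no baseline covariate. Because {20a} leaves the sidedness open, both conventions are shown below.

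**Step 2: effect of adjustment.** In a linear model, adjusting for a baseline covariate multiplies the residual variance by 1 - rho^2. The effective standardised difference becomes d / sqrt(1 - rho^2).

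- rho = 0.3: variance factor 1 - 0.09 = 0.91; sqrt = 0.954; effective d = 0.36 / 0.954 = 0.377.
- rho = 0.5: variance factor 1 - 0.25 = 0.75; sqrt = 0.866; effective d = 0.36 / 0.866 = 0.416.
- rho = 0.7: variance factor 1 - 0.49 = 0.51; sqrt = 0.714; effective d = 0.36 / 0.714 = 0.504.

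**Step 3: power at 124 per arm, d = 0.36, t-test basis.**

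| rho | Two-sided | Gain (points) | One-sided | Gain (points) |
|---|---|---|---|---|
| 0 (unadjusted) | 0.806 | – | 0.881 | – |
| 0.3 | 0.841 | 3.5 | 0.906 | 2.5 |
| 0.4 | 0.869 | 6.3 | 0.925 | 4.4 |
| 0.5 | 0.903 | 9.7 | 0.947 | 6.6 |
| 0.7 | 0.977 | 17.1 | 0.990 | 10.9 |

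The confidence interval would be about 5% narrower at rho 0.3 (1 - 0.954) and about 13% narrower at rho 0.5 (1 - 0.866).

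**Step 4: is the V1 value usable as a baseline?** Table 1 places allocation at the baseline visit, before V1. The audio starts only after intubation, and patients and staff are blinded. A value recorded before surgery therefore cannot be affected by the intervention, and V0 and V1 are both legitimate covariates.

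**The case against.** The strongest reply is that nothing here is wrong. An unadjusted comparison of randomised arms is valid, and chance imbalance is already covered by the error rate of the test. That stands: this is an efficiency point only.

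Second, {20a} leaves the confounder list open, so preoperative use is not excluded and the statistical analysis plan may name it. The quoted sentence also names no test; the t-test or Mann-Whitney reading comes from the section's general rule. Both points stand. What remains is that the article names covariates of no use for hypothesis 5 and does not name the useful one.

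Third, the gain may be modest. Long-term preoperative medication is not the same measure as nurse-controlled analgesia after surgery, the article does not say that baseline doses are quantified, and a yes/no coding would normally correlate less. The 1 - rho^2 factor also assumes a linear model, while consumption may be skewed. All of this stands, and it is why no single figure should be put forward as the gain.

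Two stronger readings are tempting:

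- **That hypothesis 5 is underpowered.** At 101 per group a two-sided t-test has power 0.721. But 101 matches a one-sided Mann-Whitney calculation, and the trial is sized at 124 per arm. There the unadjusted t-test reaches 0.806 two-sided and 0.881 one-sided; Mann-Whitney gives 0.788 and 0.868. Only the two-sided Mann-Whitney figure falls short of 0.8, and only slightly.
- **That the 3-month SF-36, iADL and GDS are likewise compared without their baseline scores.** They are collected at V0 and V9, and of the follow-up {13} says "Instead, the assessment focused on functional outcomes using the SF-36 and iADL". Yet they appear in neither the hypotheses nor Outcomes {12}, and no comparison is written for them. A condensed article may leave that to the full documents, so it is not part of this finding.

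**Conclusion.** The point holds for postoperative pain-medication consumption alone, as avoidable loss of precision. The analysis as written is valid and the stated sample size does not become wrong. For rho between 0.3 and 0.5 the gain at 124 per arm is 3.5 to 9.7 power points two-sided, or 2.5 to 6.6 one-sided. These figures rest on the plan's d = 0.36, a roughly linear relation and an assumed rho. If preoperative use is coded only yes/no, the lower end or less is more likely. The direction is certain for any appreciable correlation; the size cannot be fixed from the article.

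**What to change.** In {20a}, write a separate sentence for hypothesis 5:

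- **Main analysis:** linear regression of postoperative pain-medication consumption on randomised arm, adjusted for preoperative pain-medication use (V0/V1) and gender, the stratification factor. Use a log or rank transformation if the outcome is skewed.
- **Covariates left out:** intraoperative and postoperative drug doses.
- **Sensitivity analysis:** the unadjusted t-test or Mann-Whitney test already planned.
- **Also state:** how preoperative use is coded (a common dose unit, or yes/no if doses were not recorded) and whether the test is one-sided or two-sided.

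The cost is wording plus the work of coding preoperative medication. No new data, visits or patients are needed, and the two extra model terms reduce the residual degrees of freedom only from 246 to 244 at N = 248. The change must be fixed before anyone sees outcomes by arm. If the 3-month SF-36, iADL and GDS are to be compared between arms, the same approach with the V0 score is advisable.

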#### Interim analyses {21b}

N/a (an interim evaluation is not intended).

#### Methods for additional analyses (e.g., subgroup analyses) {20b}

Gender effects will be explored by comparing the interventions group who listened to sGS with the intervention group who listened to dGS using the above-mentioned tests. In the same manner, we also aim to explore if there is a difference between female and male speaker voice in general.

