#### Intervention description {11a}

Patients will be randomized with permuted block randomization that stratifies for their gender into a control and a intervention group within a 1:1 ratio. Intervention group will be further randomized 1:1 into a group that listens to audio content spoken by a voice that matches their gender and into a group that listens to a gender incongruent voice. The audio intervention is standardized and developed according to principles of therapeutic suggestion. We used the original text from Nowak et al. [11] as a blueprint for our intervention but adjusted it slightly to match our intentions. With the help of a soundcheck track volume will be set to a comfortable but clearly audible level before induction, with adjustments if necessary, prior to loss of consciousness. The audio content is structured into two segments. The initial segment begins after the intubation of the patient is being completed and therefore after loss of consciousness. It runs continuously (repeatedly) until approximately 15 min before the initiation of the extubation stage. The following text extracts are drawn from the first audio track (translated from the original German suggestion):

Positive suggestions to prevent delirium

*You are now sleeping soundly and deeply and can relax and rest, recover and recharge your batteries, because you are safe and well protected. Everything you hear, see, and feel contributes to your well-being. This allows your body to focus entirely on its self-healing powers. And we are by your side. You hear my voice, it accompanies you, you can concentrate fully on it, because what I tell you is important for you, important for your well-being and your healing.*

Positive suggestions to prevent pain:

*You will feel carefree and unaffected in the hours and days following the operation. You will feel calm, warm, relaxed, and content. Everything you feel will be good for your well-being. It will show you that your body is working hard to repair itself, restore balance, and return everything to normal. Your recovery can progress, unstoppable. Further and further.*

Positive suggestions to prevent PONV:

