### Assignment of interventions: allocation

#### Sequence generation {16a}

Included patients will be divided as follows: 1:1 (intervention vs. control group) and within the intervention group 1:1 to a speaker with the same gender (sGS) vs. a speaker with a different gender (dGS). Thus, the only factor influencing assignment is patient gender.

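### Pooling over patient gender mixes the voice effect with the congruence effect in the exploratory voice analyses, unless women and men are enrolled in equal numbers

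*Protocol article*

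**What the plan says.** Allocation is described in the protocol article under Intervention description {11a}, where the first step reads: "Patients will be randomized with permuted block randomization that stratifies for their gender into a control and a intervention group within a 1:1 ratio". Sequence generation {16a} adds the second step: "within the intervention group 1:1 to a speaker with the same gender (sGS) vs. a speaker with a different gender (dGS". Implementation {16c} specifies separate randomisation lists for men and women, and gives the gender–voice question as the reason for stratifying.

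The hypothesis is number 7 in Objectives {7}: "The above-mentioned effects differ depending on whether the subjects hear a speaker’s voice according to their own gender or not".

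The analysis is in Methods for additional analyses {20b}, which says: "Gender effects will be explored by comparing the interventions group who listened to sGS with the intervention group who listened to dGS". The section relies on the tests already named, and continues: "we also aim to explore if there is a difference between female and male speaker voice in general". Those tests are in Statistical methods {20a}: chi-square for binary outcomes and, for the rest, "Continuous non-parametric variables will be analyzed with Mann–Whitney *U* tests, and parametric variables with Student’s *t*-test". The regressions in {20a} name medication covariates and confounders chosen in advance. They name no voice term and no gender-by-voice term.

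Objectives {7} and Outcomes {12} label this work exploratory. Implementation {16c} calls it a secondary analysis planned in advance.

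**The concern.** The intervention arm is a two-by-two layout of patient gender by speaker gender. The same-gender group (sGS) is women hearing the female voice plus men hearing the male voice; the different-gender group (dGS) is the reverse. If most patients are women, sGS mostly hears the female voice and dGS mostly the male voice. A difference between the two recordings then shows up as a difference between matched and mismatched listeners. The reverse also holds: a true congruence effect shows up in the female-versus-male comparison.

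Stratifying by gender balances the groups within each gender. It does not make the genders equal in number, and the article states no quota. At stake is the reading of hypothesis 7. A better recording could be reported as a benefit of matching, or a real congruence effect could be diluted when the two effects have opposite signs.

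**Working it through.** **Inputs from the article.** Allocation is 1:1 to intervention or control and then 1:1 to sGS or dGS ({11a}, {16a}); I take the second split to hold within each gender, as the separate lists in {16c} imply. Sample size {14} gives an effect of 0.325 for pain intensity, a total of 248, an addition of 10% and a target of 280. The article gives no figure for the voice contrasts themselves.

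**Group size.** The 248 reproduces as a one-sided 5% Mann–Whitney calculation (efficiency 3/π, effect 0.325, power 0.8): 124 per group. Then 248 × 1.10 = 272.8, hence 273, rounded up to 280. The intervention arm has 280/2 = 140 patients, so sGS and dGS have 70 each.

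**Assumptions.** The article states neither a gender split nor a voice effect. I take splits of 50:50, 60:40 and 70:30. The voice effects are 0.325 SD (the size of the trial's whole assumed pain effect), half of that (0.1625 SD), and 10 points on delirium (20% versus 10%).

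**Algebra.** Let D_w and D_m be the female-minus-male voice differences in women and in men. Define v = (D_w + D_m)/2 and c = (D_w − D_m)/2, so that D_w = v + c and D_m = v − c. With w the share of women:

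- sGS − dGS = w·D_w − (1−w)·D_m = c + (2w−1)v
- female − male voice = w·D_w + (1−w)·D_m = v + (2w−1)c

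This is exact for means and for risks. A main effect of patient gender cancels, because voice is allocated 1:1 within gender.

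**Size.** Rejection rates are for the two-sided 5% sGS-versus-dGS test, 70 versus 70, with c = 0.

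| Women | 2w−1 | sGS−dGS from a 10-point voice effect | v = 0.1625 SD | v = 0.325 SD | Delirium 20% vs 10% |
|---|---|---|---|---|---|
| 50% | 0 | 0 points | 5.0% | 4.6% | 4–5% |
| 60% | 0.20 | 2 points | 5.4% | 6.3% | 6.0% |
| 70% | 0.40 | 4 points | 6.7% | 11.1% | 9.7% |

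The 0.1625 SD column is a normal approximation. At 60:40 the shift is 0.20 × 0.1625 / √(2/70) = 0.0325/0.1690 = 0.19 standard errors; at 70:30 it is 0.065/0.1690 = 0.38. The 0.325 SD column (20,000 runs) and the delirium column (40,000 runs) are simulated.

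**Dilution.** At 60:40 with c = 10 points and v = −10 points, sGS − dGS = 10 − 0.20 × 10 = 8 points.

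**Equal-weight contrast.** Its variance is σ²(1/n_w + 1/n_m), against 4σ²/140 = 0.02857σ² for the pooled contrast.

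- 60:40: 1/84 + 1/56 = 0.02976; √(0.02976/0.02857) = 1.02
- 70:30: 1/98 + 1/42 = 0.03401; √(0.03401/0.02857) = 1.09

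In simulation under a pure voice effect, estimating both effects together gave a mean congruence estimate of about zero and rejection rates of 4.8% to 5.2% at every split.

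**The case against.** The strongest reply is that sGS versus dGS is a randomised comparison and needs no repair. Hypothesis 7 asks whether effects differ by whether the voice matches the patient's gender. If 70% of patients are women and the female recording is better, giving everyone a matched voice really does improve the average outcome. Rejecting equality is then not a type I error for that question. This stands: a reader might infer that the pooled test is biased or invalid, and the article does not support that. What fails is the further step from a matched-versus-mismatched difference to an effect of congruence itself.

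A second reply is that large distortions need large voice effects. At 0.5 SD the test would reject in about 8% of trials at 60:40 and 20% at 70:30, but 0.5 SD exceeds the whole treatment effects assumed in {14} (0.325 and 0.36). The 10-point delirium effect is likewise most of the 12.5 points assumed there for the intervention. This also stands, and it keeps the point small.

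Third, both contrasts are planned, so a dominant voice effect would usually be seen. At 60:40 and 0.5 SD the voice test rejects in about 83% of trials and the congruence test in about 8%. That helps a careful reader but does not separate the two effects.

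Finally, model terms for an exploratory analysis can be left to an analysis plan. Here, though, {20b} names the comparison and the tests, and those do not isolate congruence.

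**Conclusion.** The point holds as a modest one. The two comparisons in {20b} each estimate a mixture of voice and congruence, with mixing factor 2w−1. The factor is zero only with equal numbers of women and men, which the article does not secure. At assumed splits of 60:40 and 70:30 a fifth and two fifths of one effect enter the other. With no congruence effect, the sGS-versus-dGS test then rejects in about 6% and 11% of trials for a voice effect of 0.325 SD, about 5% and 7% for half that, and about 6% and 10% for the 10-point delirium effect.

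Two stronger readings are not supported. The mixing does not touch the primary delirium comparison or any other intervention-versus-control comparison, because it arises only inside the intervention arm. Nor is it confounding by patient gender, because randomisation within gender removes that main effect. Adding patient gender alone as a covariate would therefore not cure the mixing.

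**What to change.** In {20b}, replace the two pooled tests by within-gender estimates in the intervention arm. For each outcome, estimate the female-minus-male voice difference separately in women and in men, as a risk difference for binary outcomes and a mean difference for continuous ones. Report half of the women's difference minus the men's as the congruence effect, and the equal-weight average of the two as the voice effect. Give each a confidence interval and label both exploratory. The pooled sGS-versus-dGS contrast may be kept if it is described as the effect of matching in the enrolled gender mix.

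If a logistic model is also fitted, state that its interaction is on the log-odds scale. With unequal baseline risks, a voice effect that is additive in risk gives a non-zero interaction there. For assumed risks of 7% versus 17% in women and 15% versus 25% in men, the voice effect is 10 points in both, but the log odds ratios are about 1.00 and 0.64.

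The cost is a few sentences and no new data. The standard error is about 2% larger than for the pooled contrast at 60:40 and about 9% larger at 70:30. Delirium estimates will be sparse: at an assumed 15% risk there are about 0.15 × 140 = 21 events over four cells.
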